#### Data Collection

This electronic survey will be conducted anonymously using the “evaluation system software” of BFH-DHP (EvaSys, Electric Paper EvaluationssystemeGmbH), which is typically used for quality control of lectures, seminars, and other educational products. The validated iPAQ-SF and bMDSC questionnaires will be transferred within the EvaSys-framework to assess participants’ physical activity and nutritional habits. Additional questions on alcohol consumption and sleep behavior will also be added to the survey.

The first survey will be conducted electronically. After closing of the 1-week survey period by the end of April 2020, the data collected will be merged and automatically extracted into an Excel spreadsheet for further analyses. The first survey will be analyzed as a cross-sectional study, in accordance with the official guidelines to analyze iPAQ-SF and adapted bMDSC. The survey results will be subjected to analyses as described in the Statistical Analyses section.

The second survey in May 2021 will also be analyzed as a cross-sectional study using the same procedures as used for the analysis of the first survey in 2020. In addition, a subgroup analyses of participants who volunteered in both surveys will allow for group comparison (during confinement versus after confinement).

#### Data Management

Data management will be performed on the BFH-DHP server. The EvaSys system will automatically store data collected from all study participants as comma separated variables (.csv) files. All data files will be imported and merged to a single data file in Excel (2018; Microsoft Corp).

Data cleansing will be performed by one researcher (JT) who will check and solve for example dot-comma decimal signs incompatibilities and to control plausibility of the data (ie, range checks). The iPAQ-SF data-cleansing guidelines will strictly be adhered to, that is, participants with incomplete (missing) data or those who responded “don’t know” will be removed from the analyses.

Data analyses will be carried out in 2 steps. First, data on physical activity, nutritional habits, alcohol consumption, and sleeping habits will be separately analyzed. Second, an explorative correlational analysis will be conducted, including only those participants with a complete set of data for all lifestyle habits under evaluation. Subgroup analyses will be conducted to compare differences in the outcomes between health profession divisions or between students’ academic levels (ie, BSc and MSc) and employee status.

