### Eligibility Criteria

All students (N=1300; 88% female and 12% male) enrolled in programs at the Bachelor of Science and Master of Science levels as well as all academic and nonacademic employees of BFH-DHP are eligible and will be invited to participate in this comprehensive, web-based survey. BFH-DHP runs these educational programs in the fields of nursing, nutrition and dietetics, midwifery, and physiotherapy. Individuals that are not employed or enrolled at the university will not be eligible for this study.

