#### Statistical Analyses

Parametric and nonparametric statistics will be used to report results from both surveys and to compare survey results with reference values obtained from the general population during pre–COVID-19 conditions. For descriptive analyses, central tendencies will be expressed as means or medians, and variation will be expressed as SD and 95% CI or interquartile ranges (25th and 75th percentiles), respectively. Kruskal-Wallis tests with posthoc Bonferroni corrections will be used to assess differences between independent groups. Results will be presented as frequency tables or as figures with boxplots.

For the explorative correlation analysis, health profession divisions, students’ academic level, and employee status will be recoded as follows: nutrition and dietetics = 1, midwifery = 2, nursing = 3, physiotherapy = 4, BSc = 1, MSc = 2, and employee = 3. The Spearman rank order correlation coefficient will be used to assess associations between the different variables under analysis. Results will be presented in a correlation matrix.

Statistical analyses will be conducted using SPSS software (version 26.0; IBM Corp.). Statistical significance will be set at the 5% level of error.

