## Results

This longitudinal study was started during the lockdown in Switzerland, in mid-April 2020 and will be completed in May 2021. The first phase of the study is underway, and data from 823 participants will be evaluated.

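### Divisions and BSc/MSc/employee status are tested one factor at a time, which is valid as unadjusted description but cannot tell a division difference from a difference in student-employee mix, or the reverse

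*Protocol article*

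**What the plan says.** Data Management sets out the group comparisons in one sentence: subgroup analyses are to "compare differences in the outcomes between health profession divisions or between" the student levels (BSc and MSc) and employee status. Statistical Analyses supplies the test: "Kruskal-Wallis tests with posthoc Bonferroni corrections will be used to assess differences between independent groups". The level is fixed there too: "Statistical significance will be set at the 5% level of error".

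Both factors are recorded for each respondent. Statistical Analyses gives their levels as "nutrition and dietetics = 1, midwifery = 2, nursing = 3, physiotherapy = 4, BSc = 1, MSc = 2, and employee = 3". The other association method is also described without adjustment: "The Spearman rank order correlation coefficient will be used to assess associations between the different variables under analysis".

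The population is mixed. Under Eligibility Criteria it covers BSc and MSc students in four fields, "as well as all academic and nonacademic employees of BFH-DHP are eligible". No headcount by division and status is given. The Results section says that "data from 823 participants will be evaluated" from the first survey. Data Collection applies the same cross-sectional procedures to the second survey, so the point arises twice.

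**The concern.** Kruskal-Wallis takes a single grouping factor and no covariates. The article names two factors measured on the same people, tests each by itself, and states no stratified, adjusted or cross-classified analysis. If one division has more employees than another, and employees differ from students in physical activity, diet or sleep, the division test picks up that difference in mix. Likewise, if one division differs and contributes an unusual share of the employees, the status test picks up the division difference. Bonferroni correction of the pairwise tests deals with multiplicity and does nothing about this.

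What is at stake is interpretation. The Introduction and Discussion say the results should help institutions inform and counsel students and employees. The student-employee contrast bears directly on that use, and division mix can distort it. The Discussion covers selection bias, information bias and missing illness data, but not this.

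The point concerns the planned group tests. It is separate from the numeric coding of categories in the correlation matrix, and correcting that coding would not resolve it.

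**Working it through.** The article states no figure on this point, so there is nothing to reproduce. The check asks how often the planned division test rejects when division makes no difference within status.

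**Inputs from the article:** N = 823 (Results); four divisions; two-sided or not is not stated, but the omnibus test at 5% is clear (Statistical Analyses).

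**Assumed inputs, since the article gives none:** four equally sized divisions; status reduced to employee versus student; employee shares by division as listed below; an employee shift δ of 0.3 or 0.5 SD on the log scale. A separate BSc/MSc effect was not simulated, though the same reasoning applies to it.

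**Hand check by a noncentral chi-square approximation, shares 10/20/30/40%, δ = 0.5:**
- Mean share = 0.25. Variance of the shares = (0.0225 + 0.0025 + 0.0025 + 0.0225)/4 = 0.0125.
- Between-division variance = 0.5² × 0.0125 = 0.003125.
- Within-division variance = 1 + 0.5² × (0.09 + 0.16 + 0.21 + 0.24)/4 = 1 + 0.25 × 0.175 = 1.04375.
- Noncentrality = 823 × 0.003125/1.04375 = 2.46. Multiplied by 3/π = 0.955, the efficiency of rank tests for a normal shift, it is 2.35.
- Probability that a chi-square on 3 df with noncentrality 2.35 exceeds 7.81: 22%.
- With δ = 0.3 the noncentrality is 0.87 and the probability is 11%.

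**Simulation (2000 replicates per setting, log-normal outcome), rejection rate of the division Kruskal-Wallis test with no division effect within status:**

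| Employee share by division | δ = 0.3 | δ = 0.5 |
|---|---|---|
| 20/20/20/20% | 5.7% | 5.7% |
| 15/20/20/25% | 6.0% | 6.6% |
| 10/20/20/30% | 7.3% | 11.9% |
| 10/20/30/40% | 10.4% | 22.2% |
| 10/10/10/50% | 22.1% | 48.5% |

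The Monte Carlo standard error at 5% is √(0.05 × 0.95/2000) = 0.5 percentage points, so the equal-mix row is compatible with 5%.

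**Reverse direction:** no status effect, one division (the fourth listed) shifted by 0.3 / 0.5 SD. The status test rejects, in the same row order, in 4.9% / 5.4%, 5.0% / 7.0%, 8.2% / 15.8%, 10.4% / 21.8% and 34.0% / 70.2% of runs.

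**With both factors in one rank-based additive model:** division adjusted for status rejects in 4.5% to 5.7% of runs, and status adjusted for division in 4.4% to 5.2%, across all these settings.

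**Size of the apparent difference:** the largest gap between two divisions due to mix alone is the range of shares times δ. For 10/20/30/40% and δ = 0.5 it is (0.40 − 0.10) × 0.5 = 0.15 SD. For 15-25% it is 0.10 × 0.5 = 0.05 SD.

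**The case against.** The strongest reply is that the plan only sets out to compare outcomes between divisions, which is a marginal question. If the mix differs, the divisions' marginal distributions do differ, and Kruskal-Wallis is right to detect it. This stands. The rejections above are false positives only for the question of whether division matters within status. A reader might infer that the Kruskal-Wallis test is itself wrong or has an inflated type I error. The article does not support that, since it never claims an effect of division independent of status.

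A reader might also infer that division differences will be used to direct counselling, so that advice would reach the wrong division. The Introduction and Discussion speak of students and employees and do not mention targeting by division.

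The size rests wholly on assumed shares and shifts. It vanishes with equal mixes and is slight at 15-25%. The step that names a division pair is the Bonferroni post hoc test, which flags somewhat less than the omnibus test: any pair in 17.8% of runs at 10/20/30/40% and 0.5 SD. These are also subgroup comparisons, not the main objective. All of this stands and limits the weight of the point.

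Adjustment is also only partial. Study Setting says that no sociodemographic characteristics could be given in the first survey, so age and sex stay uncontrolled there. That is a reason for careful wording, not for leaving out the two factors that are recorded.

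Finally, a condensed article may leave a supporting model to a fuller plan. But the article does fix the comparisons and the test, and it attaches a significance level and pairwise contrasts to them. The comment is on that stated choice.

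**Conclusion.** The point holds as a cheap improvement to the subgroup analyses. As planned, each one-way test is a valid unadjusted comparison, but neither can support a statement that a difference belongs to division rather than to status, or the reverse. How much this matters cannot be known without the division-by-status headcount. Under the assumptions above, the division test rejects in about 5-6% of runs with equal mixes, 6-7% with employee shares of 15-25%, and 10-22% with shares of 10/20/30/40% and an employee shift of 0.3-0.5 SD. Steeper imbalance gives more. Analysing the two factors together brings the rate back to about 4-6% for either factor, but it does not remove confounding by characteristics that were not collected.

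**What to change.** 1. Report the division-by-status table of respondents for each survey.
2. Keep the Kruskal-Wallis tests and boxplots, labelled as unadjusted.
3. For each outcome, add an analysis with division (four levels) and status (BSc, MSc, employee) together, both as unordered categories. Either a rank-based two-factor model or a rank test of one factor stratified by the other will serve (van Elteren where two groups are compared). Apply the Bonferroni correction to the adjusted pairwise contrasts.
4. Base any statement that a difference belongs to division or to status on the adjusted result. State that age and sex were not collected in the first survey and remain uncontrolled there.

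Suggested wording: *One-way comparisons of divisions and of status groups are unadjusted. For each outcome, division and status will also be analysed jointly as unordered factors, with Bonferroni-corrected contrasts, and attribution of a difference to either factor will rest on this analysis.*

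Cost: no new data, a few sentences of text and one more model per outcome. Sparse division-by-status cells may need merging, and any employees who belong to no division would have to be excluded from the joint analysis.

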#### Statistical Analyses

Parametric and nonparametric statistics will be used to report results from both surveys and to compare survey results with reference values obtained from the general population during pre–COVID-19 conditions. For descriptive analyses, central tendencies will be expressed as means or medians, and variation will be expressed as SD and 95% CI or interquartile ranges (25th and 75th percentiles), respectively. Kruskal-Wallis tests with posthoc Bonferroni corrections will be used to assess differences between independent groups. Results will be presented as frequency tables or as figures with boxplots.

For the explorative correlation analysis, health profession divisions, students’ academic level, and employee status will be recoded as follows: nutrition and dietetics = 1, midwifery = 2, nursing = 3, physiotherapy = 4, BSc = 1, MSc = 2, and employee = 3. The Spearman rank order correlation coefficient will be used to assess associations between the different variables under analysis. Results will be presented in a correlation matrix.

Statistical analyses will be conducted using SPSS software (version 26.0; IBM Corp.). Statistical significance will be set at the 5% level of error.

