**Conclusions:**

The findings of this survey will provide information about the impact of confinement during the COVID-19 crisis on the physical activity, nutritional habits, and sleep behavior of students and employees of a Swiss institute.

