Lifestyle habits such as physical activity, nutritional habits, and sleep behavior of university lecturers and students during such an extraordinary period of confinement and social distancing have not been studied to date. However, there is ample evidence describing the positive effects of adequate physical activity as well as the negative effects of physical inactivity on human health [1-6]. During this nearly 2-month-long lockdown period, all sports infrastructure in Switzerland was forced to close. Although regular access to fitness clubs and sports facilities was no longer possible, individuals were allowed to continue walking, jogging, and cycling. Food shops, however, remained open during this confinement period, and Swiss residents were allowed to go outside for food supply while adhering to the recommended preventive measures (eg, maintaining safe physical distance). The positive relationship between healthy nutritional habits as well as good sleep behavior and improved human health has been well documented in the literature [7-9].

Because the COVID-19 pandemic is caused by a novel coronavirus strain, and vaccination and effective treatment options are currently lacking, it is difficult to predict how the pandemic will develop. Increased knowledge about lifestyle habits of students and employees of the Department of Health Professions (DHP) at BFH (BFH-DHP) during such an extreme confinement situation may help Heads and Deans of academic institutions to inform or counsel their students and employees during a similar situation, or in case of another outbreak, in the future. However, owing to the uniqueness of the ongoing COVID-19 crisis and its societal impact, such knowledge is currently lacking.

This longitudinal observational study will examine the impact of COVID-19 confinement on lifestyle habits such as physical activity, nutritional habits, and sleep behavior among students and employees of the BFH-DHP (Switzerland) during the 2-month confinement period and social distancing and 1 year after confinement.

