## Methods

### Study Setting

This study follows a cohort study design and will be carried out at BFH-DHP in Switzerland. Figure 1 illustrates the flow diagram for the research design used in this study. This project is an interdisciplinary cooperation involving colleagues from the Departments of Nutrition and Dietetics and Physiotherapy of BFH-DHP. The contents of the survey will be developed at an interprofessional level.

This cohort study comprises 2 defined study periods: The first study period was in the end of April 2020, when the Swiss Federal Council declared the COVID-19 pandemic as an “extraordinary situation.” The first study was cross-sectional, consisting of an anonymous web-based survey. For the first survey, a questionnaire was sent to the staff and students of all 4 divisions of the institute during the COVID-19 confinement period. The participants’ responses were anonymous, in accordance with the data privacy policy of Switzerland [10]. Participants were not allowed to provide any personal information or other sociodemographic characteristics and living status. Participants could stop and exit the survey at any stage before completion. Anonymous survey procedures are known to yield higher disclosure rates of sensitive or stigmatizing information than nonanonymous procedures. Moreover, higher disclosure rates have traditionally known to be associated with more accurate results than lower disclosure rates [11].

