The results of this survey may have important public health impacts. They may empower heads of universities and higher education institutions to better prepare, inform, and counsel their students and employees on maintaining healthy lifestyle habits that may prove useful, for example, in case of an upcoming second wave of COVID-19 or a sudden outbreak of a serious new viral epidemic or pandemic in the future. Action plans for workplace health promotions may be developed with a special focus on digital dissemination routes to reach students and employees in their home-office settings.

Several biases can occur in cohort studies, which should be reduced. For instance, a selection bias resulting from the approach used to select or observe study participants, which may influence the relationship between exposure and outcome. To avoid this type of bias, this study will recruit persons from only a single institution, ie, BFH-DHP. Second, an information bias could originate either from the individuals being observed, observers, or instruments used to evaluate the results. In prospective cohorts, information bias can usually be easily avoided since measures can be taken during scheduling by including all variables in the registration forms (instruments) so that no variables of interest are overlooked.

Nevertheless, this study has limitations. The survey does not collect any data about illnesses among participants during the first phase, which could likely influence a change in the targeted behaviors.

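### The only pre-COVID comparator is general-population reference values, so a difference from them in this mainly female health-profession frame, with no sex or age recorded in 2020, cannot be attributed to confinement

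*Protocol article*

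**What the plan says.** All references are to the protocol article.

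- **Aim and conclusion.** The Introduction says the study "will examine the impact of COVID-19 confinement on lifestyle habits such as physical activity, nutritional habits, and sleep behavior". The Abstract's Conclusions paragraph says the findings "will provide information about the impact of confinement during the COVID-19 crisis" on these habits.
- **Comparator.** Statistical Analyses plans to use parametric and nonparametric statistics to report both surveys and to "compare survey results with reference values obtained from the general population during" pre-COVID-19 conditions. Significance is set at 5%.
- **Frame.** Eligibility Criteria gives 1300 students, "88% female and 12% male", in nursing, nutrition and dietetics, midwifery and physiotherapy, plus all employees.
- **2020 covariates.** Study Setting says: "Participants were not allowed to provide any personal information or other sociodemographic characteristics and living status". Second Survey adds gender and age in 2021 only. The ethics section says that the survey software cannot trace respondents.
- **Groupings.** Data Management and Statistical Analyses name division, academic level and employee status. Sex and age are not among them.
- **Second contrast.** Second Survey and Data Collection plan a comparison of habits during and after confinement.

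**The concern.** To speak of an impact of confinement on the basis of reference values, one needs values that show what these people would have reported without the lockdown. General-population values do not show that. The frame differs from the general population in sex mix, probably in age, and in professional interest in health, and would do so in any year.

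An observed gap, or its absence, could therefore come from composition. The direction is not known in advance. If men report more activity than women, a mostly female sample would look less active even with no lockdown effect, which resembles the decline that the Discussion hypothesises. Greater health orientation could hide a real decline. Because the 2020 records hold neither sex nor age, no respondent-level adjustment can separate these explanations afterwards.

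**Working it through.** **Step 1. Is there any other pre-COVID baseline?**

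- The primary outcome (short-form iPAQ) covers the last 7 days, so in April 2020 it covers confinement only.
- The diet screener asks about the past year. This mixes time before and during confinement and gives no separate baseline.
- The second survey comes a year later. It is a post-confinement comparator.

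The reference values are therefore the only pre-COVID comparator described.

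**Step 2. Can 2020 respondents be adjusted for sex or age?** No. Neither was collected in 2020. Both are collected in 2021, but without tracing they cannot be attached to 2020 records. Division, academic level and employee status remain usable.

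**Step 3. How far could sex mix alone move the comparison?** The plan states no SD, effect size or precision for this comparison, so there is no figure to reproduce. What follows is illustration.

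Inputs from the document: 88% female among 1300 students; more than 1500 eligible staff and students (Discussion); 823 participants (Results); 5% level (two-sided assumed).

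Assumed, not in the document: a 50% female reference population; a male-female difference of 500 to 1000 MET-min/week; an SD of 2000 to 3000 MET-min/week; a reference value treated as fixed.

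Shift = (female share in sample − female share in reference) × sex difference.

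- At 88% female: 0.38 × 500 = 190; 0.38 × 1000 = 380.
- Lower share: 0.88 × 1300 = 1144 female students. Taking 1500 as the total and every employee as male gives 1144/1500 = 76.3%. The shift is then 0.263 × 500 ≈ 131 to 0.263 × 1000 ≈ 263.
- Most extreme response pattern: if all 200 remaining staff and all 156 male students were among the 823, female students would be (823 − 200 − 156)/823 = 467/823 = 56.7%. With all staff male, the shift would be only about 34 to 67.

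95% half-width of a sample mean = 1.96 × SD/√823:

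- SD 2000: 137
- SD 2500: 171
- SD 3000: 205

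**Step 4. If a one-sample test were run against an unstandardised value.** Let d be the sex difference in SD units and t = (female share − 0.50) × d × √823. With no confinement effect, the chance of p < 0.05 is Φ(−1.96 + t) + Φ(−1.96 − t).

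| Assumed d | 88% female | 76.3% female |
|---|---|---|
| 0.1 | 19% | 12% |
| 0.2 | 59% | 33% |
| 0.3 | 90% | 62% |

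The nominal rate is 5%. Differences in age and health orientation are not included and could add to the shift or offset it.

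**The case against.** Several objections have force.

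- **The study has a second contrast.** A reader might infer that the whole impact claim rests on the reference values. It does not: the comparison of 2020 with 2021 uses the same institution and questionnaire and does not depend on general-population composition. This stands and limits the point to the reference-value comparison. It does not rescue that comparison, because 2021 gives no pre-COVID baseline.
- **The plan does not say which values or which test.** A reader might infer a significance test against crude population values. The article does not say whether the values will be age- or sex-specific, and the only group test it names, Kruskal-Wallis, is for independent groups. A condensed article may leave the choice of tables to a fuller document. What stands is that the stated comparator is the general population and that respondent-level sex and age for 2020 cannot be recovered by any later document.
- **88% describes enrolled students.** It should not be read as the sex mix of the 823 participants, which is unknown and may include employees.
- **The magnitude is assumed.** At the low end the shift falls inside sampling error: 190 against 205, or 131 against 137. This stands; the figures show that the shift can matter, not that it does.
- **The bias discussion.** A reader might take the Discussion's phrase "so that no variables of interest are overlooked" as a claim that this study has avoided information bias. The sentence is a hedged general remark about prospective cohorts, and information bias is a different problem from composition. It is not part of this point.

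**Conclusion.** The point holds for the reference-value comparison. A difference between the 2020 results and general-population values, or the lack of one, cannot be attributed to confinement, because composition is an equally available explanation and the 2020 data cannot separate the two. This conclusion rests on the document's own statements and not on the arithmetic.

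The size is illustrative. Under the stated assumptions, sex mix alone shifts the comparison by 190 to 380 MET-min/week at 88% female and about 130 to 260 at 76%, against a 95% half-width of 137 to 205. It is thus of the same order as sampling error or larger over much of the range, and negligible only if the respondents' sex mix is close to the reference or the sex difference is small. The net direction, once age and health orientation are included, is unknown. The change should be made before the reference-value comparison is reported.

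**What to change.** 1. **Reference values.** Use sex-specific pre-COVID values for the matching age range where they exist. For students, form a weighted reference of 0.88 × the female value + 0.12 × the male value. This works directly for means and for activity-category proportions; a median needs the weighted distribution, not a weighted average of two medians. Show the unweighted female and male values alongside, since the respondents' sex mix is unknown.
2. **Employees.** Show them separately, against sex-specific values. The document gives no sex mix for them, so no weights follow from it.
3. **2021 survey.** Gender and age are recorded there, so standardise to the respondents' own composition.
4. **Reporting.** Give differences descriptively with confidence intervals. Do not test against unstandardised general-population values.
5. **Wording.** Describe this result as habits during confinement relative to standardised reference values, not as an impact of confinement. Keep the 2020-versus-2021 comparison distinct and state that it has no pre-COVID baseline.
6. **Limitations.** Add that survey 1 recorded no sex or age and that the sex mix of its respondents is unknown.

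The cost is a weighted calculation and some rewording; no new data are needed. The causal claim becomes weaker. Confounding by health orientation and by differential response remains, because weighting to the enrolled 88/12 mix does not recover who answered.

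### Single-step Bonferroni is fixed for the pairwise comparisons, although Holm's step-down keeps the same 5% family-wise control and finds second and later true differences more often (cheap improvement, lowest severity)

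*Protocol article*

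**What the plan says.** The Statistical Analyses section names the method: "Kruskal-Wallis tests with posthoc Bonferroni corrections will be used to assess differences between independent groups". It sets the threshold as follows: "Statistical significance will be set at the 5% level of error". It does not say whether tests are two-sided.

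The groups to be compared appear under Data Management: "Subgroup analyses will be conducted to compare differences in the outcomes between health profession divisions", and also by academic level and employee status. The coding for the correlation analysis confirms the categories: "nutrition and dietetics = 1, midwifery = 2, nursing = 3, physiotherapy = 4, BSc = 1, MSc = 2, and employee = 3". That makes four divisions and three status groups.

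The only sample size given for the first survey is in Results: "data from 823 participants will be evaluated". The article states no numbers per division or status group, and no power or detectable difference for any pair.

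**The concern.** A significant Kruskal-Wallis test says that the groups differ somewhere. The pairwise tests say which divisions or status groups differ. Bonferroni holds every pair to the strictest threshold, even after other pairs have been declared different. Holm relaxes the threshold after each rejection without giving up family-wise control at 5%. For decisions on individual pairs, the stated method therefore detects less than it could at the same nominal error rate.

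What is at stake is how completely the pattern of differences is described. No result is biased. The loss can recur, because the comparisons cover several outcomes and the second survey is to be analysed in the same way as the first.

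**Working it through.** **Inputs from the article.** Four divisions; three status groups; 5% level; Bonferroni after Kruskal-Wallis; 823 respondents. There is no stated power figure to reproduce.

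**Assumptions not in the article.** Two-sided tests; normally distributed data; shifts of 0.2 to 0.9 SD between groups; group sizes either equal (about 206 × 4, or 274 × 3) or unequal (100/120/400/203, or 550/73/200).

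**Step 1: number of pairs.** m = k(k − 1)/2. Divisions: 4 × 3/2 = 6. Status: 3 × 2/2 = 3.

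**Step 2: a correction is needed.** If the tests were independent, unadjusted family-wise error would be 1 − 0.95^6 = 26.5% and 1 − 0.95^3 = 14.3%.

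**Step 3: thresholds.** Bonferroni uses 0.05/m for every pair. Holm orders the p-values and compares the i-th smallest with 0.05/(m − i + 1), stopping at the first failure.

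- Divisions: Bonferroni 0.0083 throughout; Holm 0.0083, 0.0100, 0.0125, 0.0167, 0.0250, 0.0500.
- Status: Bonferroni 0.0167 throughout; Holm 0.0167, 0.0250, 0.0500.

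The first threshold is the same, so the two methods reject at least one pair in exactly the same data sets. No later Holm threshold is stricter, so every Bonferroni rejection is also a Holm rejection.

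**Step 4: effect of one step on a single pair.** Power ≈ Φ(d√(n/2) − z), where d is the difference in SD units, n the size of each group and z the two-sided critical value.

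- n = 206, d = 0.3: 65.8% at 0.05/6, 68.0% at 0.05/5.
- n = 274, d = 0.25: 70.3% at 0.05/3, 75.3% at 0.05/2.

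**Step 5: whole procedure by simulation.** 3000 runs per scenario; pairwise rank tests (Dunn) counted only when Kruskal-Wallis was significant at 5%; total 823. Entries are Bonferroni → Holm.

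| Groups | True shifts (SD) | Average power per true pair | All true pairs found |
|---|---|---|---|
| 4 equal | one group 0.3 | 62.6% → 66.0% | 38.4% → 45.1% |
| 4 equal | two groups 0.3 | 63.2% → 68.4% | 28.9% → 40.1% |
| 4 equal | steps of 0.2 | 58.8% → 65.4% | 0.1% → 2.1% |
| 4 equal | steps of 0.3 | 79.3% → 89.8% | 9.6% → 49.2% |
| 4 unequal | one group 0.3 | 38.6% → 41.0% | 18.9% → 23.3% |
| 4 unequal | steps of 0.3 | 75.4% → 84.9% | 3.7% → 29.6% |
| 3 equal | one group 0.25 | 67.5% → 70.7% | 52.2% → 58.7% |
| 3 equal | steps of 0.25 | 78.7% → 86.6% | 40.4% → 62.2% |
| 3 unequal | one group 0.25 | 51.4% → 54.0% | 24.9% → 30.1% |
| 3 unequal | steps of 0.25 | 52.4% → 57.1% | 0.2% → 3.9% |

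Over all 14 scenarios with a true difference, the gain per true pair ran from 2.4 to 10.5 points. The gain for finding all true pairs was larger than that in 11 of the 14; the exceptions were step patterns in which finding every pair was very unlikely under either method. The chance of finding at least one true pair agreed to three decimals in every scenario (for example 84.5% for both in the first row).

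**Step 6: error rates.** With no true differences, family-wise error was 3.6% to 4.1%, the same for both methods. With some groups equal and others shifted, it was at most 2.6% under Bonferroni and 3.4% under Holm.

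**The case against.** Bonferroni after Kruskal-Wallis is conventional and keeps its error guarantee. The comparisons are subgroup analyses with no power claim attached, so no promise of the plan fails. This stands, and it keeps the point at the lowest severity.

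A reader might infer that real differences are being missed for nothing. The documents do not support that, for three reasons.

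- **The chance of rejecting at least one pair is unchanged.** Holm helps only once another pair is already significant.
- **Bonferroni buys some extra protection.** It bounds the expected number of false rejections at 5%, which Holm does not. Take three tests, one a difference that is always detected and two independent true nulls. Bonferroni expects 2 × 0.0167 = 0.033 false rejections. Holm expects (1 − 0.975²) + (0.05² − 0.025²) = 0.0494 + 0.0019 = 0.051. The article mentions no correction across outcomes, groupings and surveys, so this has modest relevance.
- **The size of the gain is not documented.** Effects and group sizes are assumed, and 823 is the count before incomplete iPAQ-SF responses are removed. With only one group differing, the gain was about 2 to 3 points.

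It can also be said that Holm is not the most powerful option. With three groups and a significant Kruskal-Wallis test, closed testing allows each pair to be tested at 0.05, and for four groups step-down methods using logical constraints improve on Holm. That is true, but it does not favour plain Bonferroni. Holm is the smallest change to the stated method.

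**Conclusion.** The point holds as an efficiency improvement, not as an error. The article fixes a valid method, and a simple alternative has the same strong 5% family-wise control under any dependence between the tests and never rejects fewer pairs. That ordering is certain. The size, about 2 to 11 points of average power per true pair and usually more for finding all true pairs, depends on the assumed shifts, normal data and group sizes, and on 823 analysable respondents. The loss is confined to second and later true differences within a family. Label: cheap improvement, lowest severity.

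**What to change.** In Statistical Analyses, replace *posthoc Bonferroni corrections* with *Holm step-down adjusted pairwise tests within each Kruskal-Wallis family*, computed from the unadjusted pairwise p-values. The adjusted value for the i-th smallest p-value is the largest of (m − j + 1) × p(j) over j = 1 to i, capped at 1.

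First-survey data are already collected and the new rule is more permissive, so record it as a dated change before the comparisons are run.

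Costs: a changed phrase and a short dated note; a small calculation on the unadjusted p-values; slightly more expected false rejections, with family-wise error still at or below 5%; and less simple simultaneous intervals. The article plans no such intervals; it presents results as frequency tables or boxplots. If intervals for pairs are added, label them as unadjusted, because they can disagree with the adjusted tests.
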